## Abstract

**Background:**

Fatigue is a common debilitating symptom of breast cancer (BC), and its treatment may result in a significant symptom burden and affect adherence to treatment. Graded exercise therapy (GET) and cognitive behavioral therapy (CBT) have separately been shown in previous studies to be beneficial for the management of cancer-related fatigue.

**Objective:**

This study’s coprimary aims are to assess the feasibility and acceptability of combining GET and CBT for the treatment of fatigue in patients with BC in Singapore. The secondary aims are to generate preliminary efficacy estimates of the combination therapy.

**Methods:**

In this randomized controlled pilot study, a total of 100 female patients with BC, with a self-reported rating of at least moderate fatigue (One-Item Fatigue Scale score ≥4), will be recruited and randomized in a 1:1 ratio to undergo a combination of GET and CBT vs GET alone (standard of care). This will include a primary cohort of 90 patients with stage I to III BC who have completed surgery and adjuvant chemotherapy (if indicated), and an exploratory cohort of 10 patients with stage IV BC undergoing systemic therapy. Acceptability will be measured using the Client Satisfaction Questionnaire, including items on cultural sensitivity. Feasibility will be measured by participant uptake, adherence to sessions, and willingness to pay for therapy sessions. Efficacy will be assessed based on quantitative measures of fatigue, treatment adherence, quality of life, and physical and functional outcomes.

**Results:**

Recruitment of participants commenced on July 14, 2025, and is projected to be completed by December 31, 2026. The primary completion date is expected to be April 30, 2027, and publication of the final results is expected by the end of 2027.

**Conclusions:**

This study will provide evidence on whether a combination of GET and CBT is feasible and acceptable for the treatment of fatigue in patients with BC in Singapore. It supports the refinement of evidence-based fatigue management guidelines and improvements in BC survivorship care.

## Introduction

Since global estimates of cancer were first published in 1984, breast cancer (BC) has remained the most frequently diagnosed cancer in women [1,2]. In 2022, there were an estimated 2.3 million new cases and 670,000 deaths from BC, with these figures projected to increase by 38% and 68%, respectively, by 2050 [3]. Systemic therapies such as chemotherapy, targeted therapies, and endocrine therapies have significantly improved overall survival in BC [4]. However, these treatments are associated with a significant symptom burden that can negatively impact patients’ quality of life (QoL) and ability to adhere to the treatment regimen, with consequent detrimental effects on treatment and survival outcomes [5].

Fatigue is a commonly reported symptom after BC treatment. In a review of fatigue in patients with BC, 66% reported the presence of some degree of fatigue, with one-third reporting that fatigue constituted an important problem [6]. For example, in the pooled analyses of the PALOMA (Palbociclib: Ongoing Trials in the Management of Breast Cancer) trials, which established the role of the cyclin-dependent kinase 4/6 inhibitor palbociclib in BC treatment, new-onset fatigue incidence rates were 23.9%, with an incidence of severe fatigue of 14.8% [7]. A separate meta-analysis found that patients who were on cyclin-dependent kinase 4/6 inhibitor–based regimens had a significant increase in all grades of fatigue, and a relative risk of 3.06 (95% CI 1.41‐6.61; *P*=.004) for high-grade fatigue [8].

As a result of fatigue and other contributory factors, suboptimal adherence to oral treatments for BC is a well-documented problem, with discontinuation ranging from 31% to 73% by 5 years of treatment [9]. Adverse events are closely related to patient adherence and persistence. A survey of patients’ experiences of cancer treatment, including patients with BC, found that 10.1% of poor adherence was directly attributed to fatigue; 27% reported severe fatigue, with 19% confirming poor treatment adherence [10]. In patients with BC receiving endocrine treatment, those with nonadherence and nonpersistence had significantly reduced event-free survival, with hazard ratios ranging from 1.39 (95% CI 1.07-1.53) to 2.44 (95% CI 1.89-3.14), and also negatively impacted overall survival, with hazard ratios ranging from 1.26 (95% CI 1.11-1.43) to 2.18 (95% CI 1.99-2.39) [11].

Current evidence supports the inclusion of exercise to manage cancer-related fatigue (CRF) during and after the completion of cancer treatment as part of standard care [12]. However, the delivery of these interventions may present challenges with patient adherence to the designed interventions. Cognitive behavioral therapy (CBT) is an evidence-based supportive intervention that has been shown to improve symptom burden and QoL in patients with BC [13]. CBT could potentially address both the cognitive and behavioral factors that could impede motivation for exercise. Thus, the addition of CBT to graded exercise therapy (GET) should have a synergistic effect in the management of fatigue in patients with BC [14].

This pilot study evaluates the combination of GET and CBT for the treatment of fatigue in patients with BC in Singapore.

## Methods

### Study Design

This is a randomized controlled, nonblinded, pilot intervention study that will enroll 100 female patients with BC with reported fatigue to receive either a combination of GET and CBT or GET alone.

### Ethical Considerations

The study will be conducted in accordance with the ethical principles that have their origin in the Declaration of Helsinki and that are consistent with Good Clinical Practice and the applicable regulatory requirements. Ethical approval was obtained from the SingHealth Central Institutional Review Board (protocol number 2025/0016). Written informed consent was obtained from all participants involved in the study.

Zoom, a cloud-based videoconferencing platform, will be used as the platform to facilitate GET and CBT teleconsultations. No data will be collected or stored using this platform. Access to Zoom sessions will be restricted to authorized members of the study team.

FormSG, a Singapore government platform for the creation of secure digital forms, will be used to collect survey responses, including both personal data (eg, name and contact details) and research data (eg, survey responses). The FormSG account and surveys will be protected by a username and password. All data collected will be stored on encrypted storage devices secured under lock and key or on a hospital-approved secure drive located within the hospital firewall. Access to the data will be limited to authorized members of the study team. Research data will be identifiable only by patient ID. The file linking patient IDs to personal identifiers will be stored separately from the research data. Participants’ privacy will be safeguarded, and personal data will not be disclosed to any third party.

### Specific Aims

The coprimary aims are to evaluate: (1) acceptability of GET and CBT, using the Client Satisfaction Questionnaire-8 (CSQ-8), including items on cultural sensitivity; and (2) feasibility of GET and CBT as indicated by participant uptake and adherence to sessions and participants’ willingness to pay for therapy sessions.

We hypothesize that at least 70% of patients with BC will find the combination of GET and CBT to be acceptable and will adhere to their therapy sessions.

The secondary aims include the following:

Assessment of preliminary efficacy in reducing fatigue using the Functional Assessment of Chronic Illness Therapy–Fatigue (FACIT-F) subscaleEvaluation of adherence to BC treatments using self-reported adherence data and estimations from dispensed medication possession ratiosEvaluation of QoL using the Functional Assessment of Cancer Therapy–General (FACT-G) questionnaireAssessment of physical activity and functional outcomes using the Godin-Shephard Leisure-Time Physical Activity Questionnaire (GLTPAQ), 6-minute walk test (6MWT), handgrip strength (HGS), and 5-times sit-to-stand test

### Eligibility Screening and Recruitment

The study cohort will include a primary group of 90 patients with nonmetastatic BC (stage I-III) and an exploratory group of 10 patients with stage IV BC. The exploratory group will be combined with the primary cohort to generate outcome estimates in a broader population with BC to facilitate future study planning. Textbox 1 details the inclusion and exclusion criteria for both the primary and exploratory groups.

Textbox 1.Inclusion and exclusion criteria.
**Inclusion criteria**
Primary groupDiagnosed with stage I to III breast cancer (BC), regardless of hormone receptor status or human epidermal growth factor receptor 2 statusCompleted surgery and any adjuvant chemotherapy (if indicated)Exploratory groupDiagnosed with stage IV BCCurrently receiving systemic therapy (including endocrine therapy, chemotherapy, targeted therapy, or immunotherapy)For both groupsAged 21 years or olderExperiencing fatigue, with a One-Item Fatigue Scale score ≥4 (at least moderate fatigue)Able to read and communicate in EnglishWilling to provide informed consent for study participation
**Exclusion criteria**
Pregnant or lactatingPresence of dementia or major psychiatric diseaseDeemed medically unsuitable by the medical team for low- to moderate-intensity exerciseUnable or unwilling to participate in video counseling sessionsPresence of uncontrolled or undiagnosed painLow blood counts: hemoglobin <8.0 g/dL, platelets <50 × 10^9^/L, absolute neutrophil count <1 × 10^9^/L, potassium <3 mmol/L, or sodium <130 mmol/LPresence of cardiovascular disease, including reduced left ventricular ejection fraction <30%, uncontrolled arrhythmias, severe coronary artery disease, severe valvular heart disease, or uncontrolled hypertension that has not been cleared by a cardiologistPresence of an active infectionAlready engaged in moderate- to vigorous-intensity physical activity

Study investigators and research assistants will screen participants based on the above inclusion and exclusion criteria and will approach eligible participants during their clinic appointments or via telephone to introduce the study. Interested participants will be screened for fatigue using the One-Item Fatigue Scale score (“How would you rate your fatigue on a scale of 0 to 10, with 0 being ‘no fatigue’ and 10 being ‘the worst possible fatigue’?”), with a score of 4 or more indicating at least moderate fatigue. This one-item scale has demonstrated convergent validity with other measures of fatigue and has been shown to be able to identify cases of fatigue meeting criteria on the FACIT-F scale [15].

### Setting

Participants will be recruited from multiple sites across Singapore: Singapore General Hospital, a tertiary hospital, the National Cancer Centre Singapore, the national oncology specialty center based at the Outram Campus, and National Cancer Centre Singapore satellite clinics at Sengkang General Hospital and Changi General Hospital.

### Experimental Design

Recruited participants will be randomized via a web-based system to either the GET-only arm or the GET plus CBT arm in a 1:1 ratio using a randomized permuted block method, with stratification by study site. The randomization list is generated by the study statistician, and block sizes are kept unknown to all other study personnel. The study schema is shown in Figure 1. Both GET and CBT sessions will be delivered remotely by trained rehabilitation physicians and clinical psychologists, respectively, via the Zoom videoconferencing platform.

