### Statistical Methods

This study combines the A’Hern single-arm decision framework with a randomized 2-arm design. The single-arm decision framework is applied to the GET and CBT arms to evaluate the coprimary aims of feasibility and acceptability in the primary study cohort of patients with stage I-III BC. The randomized 2-arm design is adopted to estimate differences in preliminary efficacy estimates between the GET and CBT arms and the GET-only arm. Sample size is estimated based on the A’Hern single-arm decision framework. Under this framework, the combined GET and CBT will be considered feasible and acceptable if at least 70% of patients in the primary study cohort score at least 24 points on the CSQ-8 survey at 3 months and attend at least 3 out of 4 sessions for GET and CBT each. No formal hypothesis testing of between-arm differences will be undertaken, as the study is not powered for comparative efficacy analyses and will focus on generating preliminary estimates of effect.

The study team considers the combination of GET and CBT worthy of further investigation if at least 70% of eligible participants randomized to the GET plus CBT arm find the therapy acceptable and adhere to their therapy sessions. Conversely, the combination therapy will not be worthy of further investigation if the acceptability and feasibility rate is less than 50%. Based on the A’Hern design, the combination of GET and CBT will be worthy of further investigation with 80% power and a 5% significance level if at least 24 of 37 participants find the therapy acceptable and adhere to their therapy sessions. With a 1:1 allocation ratio in this randomized study, a total of 90 participants will be recruited, with 45 participants in each arm, after accounting for dropout. An exploratory study cohort of 10 patients with stage IV BC is included in this study, and the total sample size is 100 participants.

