All analyses, except for safety data, will be based on an intention-to-treat approach. Safety data will be reported based on the actual intervention received by participants. Descriptive statistics will be used to summarize participants’ characteristics, the willingness-to-pay survey, safety data, and close-ended participant feedback items. Responses to open-ended questions will be analyzed using descriptive content analysis to identify common themes and illustrative examples. The primary feasibility endpoint will be estimated based on the exact method. The primary acceptability endpoint will be estimated based on a mixed effects logistic regression model. This model will include indicator variables for postbaseline assessment time points and study sites as fixed effects and patient-specific random intercepts. Continuous secondary outcome measures, including FACIT-F, Medication Adherence Scale, FACT-G, GLTPAQ, 6MWT, HGS, and 5-times sit-to-stand test, will be analyzed using mixed effects linear regression models for repeated measures. For each measure, the change in score between assessment time points within each arm and the difference in scores between the 2 arms at the various assessment time points will be estimated and reported with 95% CIs. Each mixed effects linear model will include study arm, indicator variables for postbaseline assessment time points, interaction terms between the time variables and study arm, and study sites as fixed effects and patient-specific random intercepts. Models estimating the difference in scores between the 2 arms at various assessment time points will be further adjusted for baseline score. The choice of the structure used to fit the covariance matrix of each mixed effects model will be assessed at the time of analysis. No imputation for missing data will be carried out, and all patients with nonmissing data at any one of the assessment time points will be included in the analysis. No adjustment for multiple comparisons of secondary outcome measures will be made.

Two sets of analyses will be conducted. The first set will be based on the primary study cohort, and the second set will be based on the combined primary and exploratory study cohorts. For the second set, no hypothesis testing will be conducted. The focus of this set is to generate outcome estimates in all patients with BC to facilitate future study planning.

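### The pooled stage I-III plus stage IV models carry no cohort term, and the pooled result is described more broadly than the enrolled 90:10 mix allows

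*Protocol article*

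**What the plan says.** The study enrols "a primary group of 90 patients with nonmetastatic BC (stage I-III) and an exploratory group of 10 patients with stage IV BC" (Protocol article, Eligibility Screening and Recruitment). According to the abstract's Methods, all 100 "will be recruited and randomized in a 1:1 ratio to undergo a combination of GET and CBT vs GET alone". Experimental Design gives the allocation as "in a 1:1 ratio using a randomized permuted block method, with stratification by study site". It describes no separate list or stratum for stage IV.

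Statistical Methods applies the A'Hern rule to the stage I-III cohort alone and plans for 45 per arm: "a total of 90 participants will be recruited, with 45 participants in each arm, after accounting for dropout".

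The same section lists the model terms once and then announces two sets of analyses, one on the primary cohort and one on both cohorts combined. The linear models contain arm, post-baseline time, arm-by-time, site and a patient random intercept, with baseline score added for between-arm differences. The logistic model for acceptability contains time, site and a random intercept. Neither list includes cohort or stage. The second set has no hypothesis tests, and its purpose is given as: "The focus of this set is to generate outcome estimates in all patients with BC to facilitate future study planning". Eligibility Screening and Recruitment gives the same purpose: "The exploratory group will be combined with the primary cohort to generate outcome estimates in a broader population with BC".

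**The concern.** The two cohorts enter under different criteria. Stage I-III patients have finished surgery and any adjuvant chemotherapy, while stage IV patients must be receiving systemic therapy. It is plausible, though the article gives no figure, that their fatigue and function differ over follow-up. If they do, and neither the randomisation nor the model takes account of cohort, part of the pooled arm difference reflects which arm happened to receive more stage IV patients. The pooled estimates are meant to feed later study planning, so avoidable noise in them is worth removing.

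The second issue is what the pooled number estimates. The 90:10 ratio is a recruitment quota. An overall figure weighted by that quota describes this enrolled mix. It describes a general breast cancer population only if the two stages respond alike or the mix happens to match.

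**Working it through.** **Inputs from the article.** 90 stage I-III and 10 stage IV patients; 1:1 allocation; site as the only named stratum; primary rule of at least 24 of 37 with a null rate of 50% and a target of 70%; 45 stage I-III patients per arm.

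**Assumptions.** The cohorts share blocks. The arms have 50 patients each. The stage effect on FACIT-F remaining after baseline adjustment is 5 points (range 3 to 8); the article gives no value. Dropout is 8 of 45 = 17.8%, implied by 37 evaluable out of 45 because no rate is stated.

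**Step 1: the plan's own figure.** With an exact one-sided binomial, 24 of 37 has a type I error of 4.9% at a true rate of 50% and power of 80.7% at 70%. The stated rule is reproduced.

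**Step 2: the stage IV split.** The number of stage IV patients in the GET plus CBT arm follows approximately a hypergeometric distribution (100 patients, 10 stage IV, 50 drawn), with SD 1.5.

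| Split | Probability |
|---|---|
| exactly 5:5 | 25.9% |
| 7:3 or worse, either direction | 31.8% |
| 8:2 or worse, either direction | 9.2% |

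Block size is undisclosed ("block sizes are kept unknown to all other study personnel"). Simulation with blocks of 4, or 4 and 6, over 3 or 4 sites gave the same SD of about 1.5 and 8:2 or worse in about 8% to 9% of runs. Blocking by site therefore hardly restrains the stage split.

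**Step 3: effect on the pooled arm difference.** Shift = (stage IV in one arm − stage IV in the other) / 50 × stage effect.

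| Split | Multiplier | 3 points | 5 points | 8 points |
|---|---|---|---|---|
| 6:4 | 2/50 = 0.04 | 0.12 | 0.20 | 0.32 |
| 7:3 | 4/50 = 0.08 | 0.24 | 0.40 | 0.64 |
| 8:2 | 6/50 = 0.12 | 0.36 | 0.60 | 0.96 |

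FACIT-F runs from 0 to 52.

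**Step 4: what the pooled figure weights.** For illustration only, assume feasibility of 70% in stage I-III and 40% in stage IV. The enrolled mix then gives 0.9 × 70% + 0.1 × 40% = 67%. An 80:20 mix would give 0.8 × 70% + 0.2 × 40% = 64%. The number depends on the quota, and the pooled figure alone does not show the 40%.

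**Step 5: does the split hurt the primary rule?** Retain each randomised patient with probability 37/45, apply the exact rule with type I error at most 5% at each evaluable number, and average the power. With exactly 45 stage I-III patients in the GET plus CBT arm, expected power is 76.2%. With the random stage IV split it is 76.1%. The chance of fewer than 37 evaluable is 41% and 42%, respectively. Random dropout alone has SD √(45 × 37/45 × 8/45) = 2.6, against 1.5 for the split.

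**The case against.** A reader might infer that the uneven split threatens the primary analysis, because GET plus CBT has a 37% chance of fewer than 45 stage I-III patients and power falls to 73.7% at 36 evaluable. The calculation does not support this. Power also falls when there are more patients (77.4% at 38, 74.0% at 39), so these drops come from where the integer cut-off lands. An arm above 45 is as likely as one below. Averaged over both, the cost is 0.1 percentage points, and dropout drives any shortfall. If every randomised patient is counted, which the intention-to-treat statement would allow for attendance, power is 83.6%, 80.8%, 86.1% and 83.6% at 42, 43, 44 and 45 patients.

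A reader might also infer that randomisation should now be restratified by cohort. With 10 stage IV patients over several sites and 48 patients recruited by the end of April 2026, that is a debatable trade-off. In simulation, cohort strata still gave exactly 45 in only 38% to 51% of runs.

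Nor can it be said that pooling defeats the purpose of enrolling stage IV patients, because pooling is the purpose the article declares.

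Three further points against the concern stand. Shared blocks are an inference, since the article is silent on a separate list. The imbalance arises by chance and is not systematic bias. The second set is for estimation only, baseline adjustment absorbs part of any stage difference, and the primary-cohort analyses exclude stage IV altogether. These points limit the size of the issue. They do not explain why a factor known at entry is left out of models whose terms are otherwise listed.

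**Conclusion.** The point holds as a modest improvement to the second analysis set. As listed, the pooled models contain no cohort term and cohort is not a named stratification factor, so the stage mix of the arms is left to chance. A 7:3 split or worse has a probability of about 32% if the cohorts share blocks. At 7:3 the pooled FACIT-F difference moves by 0.24 to 0.64 points if the stage effect after baseline adjustment is 3 to 8 points. That effect size is an assumption. The power of the primary rule is not materially affected.

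The wording of the pooled aim is broader than the design supports: the result describes a fixed 90:10 enrolment mix.

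**What to change.** 1. Add cohort (stage I-III versus stage IV) as a fixed effect in the models of the second analysis set. For acceptability, report the pooled percentage averaged over the enrolled mix. If about five stage IV patients in the arm are too few for a stable logistic coefficient, give the raw counts and say so.
2. Describe the pooled result as an estimate for the enrolled 90:10 mix of stage I-III and stage IV patients.
3. Show stage IV counts by arm beside the pooled results.

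The cost is one model term, a change of wording and a few table rows. Randomisation does not change, and data analysis had not begun when the article was submitted, so the terms can still be fixed in advance. A sentence saying whether stage IV patients have their own randomisation list would settle the one inference made here.
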